## Abstract

**Background:**

Stepped care is recommended and implemented as a means to organise depression treatment. Compared with alternative systems, it is assumed to achieve equivalent clinical effects and greater efficiency. However, no trials have examined these assumptions. A fully powered trial of stepped care compared with intensive psychological therapy is required but a number of methodological and procedural uncertainties associated with the conduct of a large trial need to be addressed first.

**Methods/Design:**

STEPS (Developing stepped care treatment for depression) is a mixed methods study to address uncertainties associated with a large-scale evaluation of stepped care compared with high-intensity psychological therapy alone for the treatment of depression. We will conduct a pilot randomised controlled trial with an embedded process study. Quantitative trial data on recruitment, retention and the pathway of patients through treatment will be used to assess feasibility. Outcome data on the effects of stepped care compared with high-intensity therapy alone will inform a sample size calculation for a definitive trial. Qualitative interviews will be undertaken to explore what people think of our trial methods and procedures and the stepped care intervention. A minimum of 60 patients with Major Depressive Disorder will be recruited from an Improving Access to Psychological Therapies service and randomly allocated to receive stepped care or intensive psychological therapy alone. All treatments will be delivered at clinic facilities within the University of Exeter. Quantitative patient-related data on depressive symptoms, worry and anxiety and quality of life will be collected at baseline and 6 months. The pilot trial and interviews will be undertaken concurrently. Quantitative and qualitative data will be analysed separately and then integrated.

**Discussion:**

The outcomes of this study will inform the design of a fully powered randomised controlled trial to evaluate the effectiveness and efficiency of stepped care. Qualitative data on stepped care will be of immediate interest to patients, clinicians, service managers, policy makers and guideline developers. A more informed understanding of the feasibility of a large trial will be obtained than would be possible from a purely quantitative (or qualitative) design.

**Trial registration:**

Current Controlled Trials
ISRCTN66346646 registered on 2 July 2014.

## Background

### Prevalence, impact and access

Depression is a long-term and relapsing condition and set to become the third biggest cause of the global burden of disease by 2030
[1]. Over three-quarters of all people who recover from one episode will go on to have at least one more
[2]. Lifetime prevalence has been estimated at 16.2% and rates of co-morbidity are high
[3–5]. In the UK, depression and anxiety are estimated to cost the economy £17 billion in lost output and direct healthcare costs annually, with a £9 billion impact on the Exchequer through benefit payments and lost tax receipts
[6].

Whilst there is a clear need for effective depression treatment, access to treatment is poor: results from the Adult Psychiatric Morbidity Survey 2007 indicate only 24% of people with common mental health problems receive treatment; of those, 42% receive an evidence-based psychological therapy
[7]. For people with a severe mental disorder, 35 to 50% of people in high-income countries receive no treatment
[8].

### Stepped care

To maximise access, many clinical guidelines worldwide recommend evidence-based psychological therapies for depression to be delivered at low- and high-intensity levels using a system called ‘stepped care’
[9–12]. Stepped care requires that almost all patients start with an evidence-based treatment of low-intensity as a first step
[13]. Progress is monitored systematically and patients who do not respond adequately step up to a subsequent treatment of higher intensity
[14]. Low-intensity treatments are usually defined as those treatments that require less time from a healthcare professional than a conventional treatment
[15], although intensity may also mean the time required of patients, cost and therapists’ level of expertise. In England, stepped care has been adopted by ‘Improving Access to Psychological Therapies’ (IAPT) services (
http://www.iapt.nhs.uk) which have treated 500,000 patients annually since 2008. The majority of patients receive low-intensity treatment; around 30% are either allocated directly or ‘stepped up’ to high-intensity psychological therapy
[16].

### Uncertainties

Although stepped care is widely implemented in England, based on their narrative review Bower and Gilbody caution that the equivalence and efficiency of stepped care are untested
[14]. The central tenet of stepped care is that, for most patients, low-intensity treatment is sufficient and relatively few patients need to step up. If this holds, compared with alternatives, stepped care may achieve equivalent clinical outcomes at reduced cost and increase access to treatment. However, there is insufficient evidence to support this. In a systematic review and meta-analysis of randomised controlled trials (RCTs) of stepped care, we found a moderate effect of stepped care compared with care-as-usual (n = 4580 patients, *d* = 0.34, 95% CI 0.20 to 0.48)
[17] yet care-as-usual may not be the best trial comparator. To test equivalence and efficiency, a fully powered clinical trial of stepped care compared with an alternative system which has the potential to be as clinically effective is required
[14, 17].

The National Institute for Health and Care Excellence has made a specific recommendation to conduct a fully powered trial of stepped care versus matched care for depression
[10]. Although the two systems may be as clinically effective, there are no prognostic indicators, including severity of depression itself, with sufficient power to predict response to treatment and therefore the specific treatment required for matched care
[18]. In terms of severity, a recent individual patient data meta-analysis of 2,470 patients with depression receiving low-intensity treatment has shown that patients with severe symptoms show at least as good clinical benefit from low-intensity interventions as less severely ill ones
[19]. Conversely, if cognitive behaviour therapy (CBT) as an example of an intensive psychological therapy is presently considered the ‘gold standard’ treatment for depression (effective against a number of comparators, in patients with a range of severity of depressive symptoms, in group and individual settings, and for both relapse prevention and treatment of a current episode
[10]), the key question to test equivalence and efficiency becomes "can CBT be ‘re-structured’ (as in stepped care) and achieve equivalent patient outcomes at less cost, compared with offering almost all patients high-intensity CBT alone?" Compared with matched care, there are fewer uncertainties associated with high-intensity CBT. Therefore, in our opinion, the most appropriate and robust test of the equivalence and efficiency of stepped care would be a fully powered RCT against high-intensity (intensive) psychological therapy alone.

### The need for a mixed methods feasibility study

Whilst a fully powered RCT of stepped care compared with intensive therapy is needed, a number of methodological and procedural uncertainties currently prevent such a trial: the appropriateness of potential trial methods and procedures; recruitment and retention rates; the proportion of patients who step up from low- to high-intensity psychological therapy; an estimate of treatment effects to inform a sample size calculation for the large trial; and the acceptability of stepped care.

National IAPT data confirm that, despite the average results cited above, rates of stepping up from low- to high-intensity treatments varied from 0 to 50% of patients seen across services in the first year of their operation
[20]. Services use different criteria to make clinical decisions on initial stratification and stepping up
[21]. This may reflect a lack of guidance on how stepped care should be delivered; as yet, the optimal configuration of system elements is unknown
[14, 17]. Data on current practice will not reliably inform rates of stepping in a fully powered trial.

With respect to acceptability, patients’ views of the underpinning principles and implementation of stepped care are uncertain
[14]. Equally, we are unsure of the views of administrative staff, therapists and other health professionals who are required to deliver and support stepped care
[14]. If patients and/or therapists are strongly opposed to stepped care this has implications for design and perhaps feasibility of a large RCT. In the absence of specific guidance on how to implement stepped care, views on its operationalisation will be important to inform the development of a stepped care clinical protocol for use in a large clinical trial.

Commensurate with the Medical Research Council framework for the development and evaluation of complex interventions
[22], all of the above uncertainties are appropriate to address through piloting and in a feasibility study
[23]. An issue that arises is that quantitative data alone will be inadequate. To understand what people think of potential trial methods and procedures, qualitative data will be important. Integrated with numeric data, they will provide a richer understanding of the appropriateness of those procedures. Moreover, to understand the acceptability of stepped care, qualitative data are required. Merged with quantitative data on treatment adherence, they may help explain variability in patients’ therapeutic engagement. Ultimately, the outcome of a feasibility study that encompasses the collection and integration of quantitative and qualitative data will be the information needed to design a large RCT of stepped care.

### Study purpose

The purpose of this study will be to prepare the ground for undertaking a fully powered RCT of stepped care compared with high-intensity psychological therapy alone for the treatment of depression in adults.

### Objectives

Our specific objectives will be to: (1) gather enough information on recruitment, retention, step ups and treatment effects to design a fully powered clinical trial or to determine that such a trial is not feasible; and (2) explore patients’ and therapists’ views of stepped care and the ways in which patients’ views relate to how much they engage in therapy to inform a stepped care clinical protocol for a proposed randomised trial.

### Research questions

What is the quantifiable performance of recruitment and retention methods which may be used in a fully powered trial? (Objective 1)What proportion of people who receive stepped care step up from low-intensity to high-intensity treatment or are discharged following low-intensity psychological therapy? (Objective 1)What is the variability in patient-related outcomes following stepped care or intensive psychological therapy alone and how do they correlate with patients’ baseline scores? (Objective 1)To what extent are potential recruitment methods considered appropriate by trial participants (patients), study therapists and other health professionals and administrators and how do people’s views combine with numeric data on the performance of trial recruitment methods? (Objective 1)How acceptable is stepped care to patients and therapists and how do patients’ views explain variability in the number of treatment sessions they attend? (Objective 2)

## Methods/Design

STEPS (Developing stepped care treatment for depression) uses a mixed methods embedded design
[24] in which semi-structured interviews with patients, therapists and other health professionals will be embedded within a pilot RCT of stepped care versus intensive psychological therapy alone for people with depression. Quantitative data will be used to assess the feasibility of trial recruitment, retention and clinical procedures and to inform the sample size calculation that is required for a full-scale evaluation. Semi-structured interviews will be embedded in the pilot trial and undertaken concurrently to explore what trial participants (patients) and others (for example, study therapists) think of (i) trial methods and procedures and (ii) the acceptability of the stepped care intervention. By merging qualitative and quantitative data on trial methods and procedures, we will develop a richer understanding of their feasibility and appropriateness; through the integration of qualitative and quantitative data on the acceptability of stepped care we will aim to explain variability in patients’ treatment adherence.

### Philosophical assumptions

By advocating a mixed methods design where the decision to incorporate qualitative and quantitative methods is guided by the set of uncertainties (unanswered research questions) that must first be addressed to inform a full-powered RCT, we are guided by a pragmatic philosophy: we give primary importance to the problem to be addressed and how the information we collect will be used
[25]. We will also combine deductive and inductive thinking; we will allow for a singular view and multiple views of reality in how we come to understand and interpret our findings; the motivation for the research is to inform ‘real-world’ practice in the care of adults with depression. In these respects, our views are consistent with a pragmatic worldview
[24].

### Pilot randomised controlled trial

#### Setting and participants

We will recruit participants from an IAPT service. Eligible participants will be aged 18 and older with *Diagnostic and Statistical Manual of Mental Disorders* (DSM) Major Depressive Disorder identified by standard clinical interview (Clinical Interview Schedule – Revised)
[26]. In line with the current operating criteria for IAPT services to determine who they treat and to reflect the pragmatic nature of this trial (and the fully powered evaluation) we will identify and exclude people at interview who are alcohol or drug dependent, acutely suicidal or cognitively impaired, have bipolar disorder or psychosis/psychotic symptoms. Participants will be eligible whether they are in receipt of antidepressant medication or not. Patients will subsequently be treated at the Mood Disorders Centre Accessing Evidence-Based Psychological Therapies (AccEPT) clinic facilities (see Trial Interventions section below).

#### Randomisation, allocation concealment and blinding

Participants will be allocated in a 1:1 ratio to either the stepped care or intensive psychological therapy arms stratified according to their symptom severity on the Beck Depression Inventory version I (BDI-I)
[27] (BDI-I minimal (0 to 9), mild (10 to 18), moderate (19 to 29), severe (30 to 63)). Allocation will be minimised to maximise the likelihood of balance in stratification variables across the two study arms. Concealment will be ensured by use of an externally administered, password-protected randomisation website and retaining a stochastic element to the minimisation algorithm. The computer-based allocation and website will be developed and maintained by the accredited Peninsula Clinical Trials Unit, independent of the trial. Participants’ details will be sent to the clinic administrator to alert them to assign the patient a study therapist and contact the patient to arrange treatment.

All research measures will be applied equally to both groups of participants. At baseline, the study researcher ([name]) will be blind to group allocation which will occur after this assessment. At follow-up, the researcher will be unblinded to allow her to interview patients (who have been allocated to receive stepped care) on end-treatment; interviews will occur prior to follow-up. Follow-up (and baseline) data will be self-reported. In our opinion, the risk of bias related to unblinding will be both minimal and tolerable.

#### Recruitment

Patients will be recruited via an IAPT service serving a city population. The service will write to all patients who are offered an initial assessment appointment to invite them to take part. A study summary sheet and permission for researcher to contact form will accompany each letter. Patients who complete and return their permission-to-contact form will be telephoned by the study researcher who will use a standard two-question case-finding instrument for depression
[28] to assess possible eligibility. Baseline interviews will be arranged with potentially eligible and willing participants. Interviewees will be sent a full study information sheet and flow-chart. At interview, the study will be explained in full and we will assess eligibility using the Mini-Cog
[29] to screen for cognitive impairment and the Clinical Interview Schedule (Revised)
[26]. If eligible, fully informed and consenting, patients will enter into the study. Ineligible and/or unwilling patients will continue with usual care at the IAPT service. We estimate from our recent experience managing other National Institute for Health Research mental health trials
[30–32] that we will need to send out 1,500 recruitment letters to achieve the upper limit of our sample size (see below and Figure 
1).

**Figure 1 Fig1:**
[figure not shown]
**Consolidated standards of reporting trials (CONSORT) diagram describing flow of patients through the study.**

#### Trial interventions

Clinical procedures in both arms of the feasibility trial are CBT in both low- and high-intensity variants. All treatments will be delivered at the Mood Disorders Centre AccEPT Clinic facilities (
http://www.exeter.ac.uk/moooddisorders/acceptclinic/). The AccEPT Clinic is part of the School of Psychology at the University of Exeter. It provides psychological therapies as part of the Mood Disorders Centre’s mission to develop, test and make accessible effective treatments for depression and other mood disorders. Although the AccEPT Clinic has been commissioned by the National Health Service, it is separate to and not an IAPT service; it has not previously delivered stepped care treatment for depression.

#### Stepped care

Stepped care will involve initial low-intensity CBT delivered using guided self-help (GSH) materials and, dependent on treatment response, high-intensity CBT. GSH material will be an offline version of the internet-delivered Wellbeing Course developed by the Centre for Emotional Health at Macquarie University, Sydney, Australia (http://www.ecentreclinic.org/). In some cases, the Centre for Emotional Health supplies course material by post and patients are supported by a therapist via the internet or by phone. Course effectiveness has been established
[33–35]. With the permission of Macquarie, we have adapted the Wellbeing Course for UK patients; culturally specific information and references have been replaced with equivalent for the UK. Course material is otherwise unchanged. We have consulted closely to replicate the weekly delivery of the online course in how we will provide patients with pdf or paper documents. Each week for 5 weeks we will email or post patients a Lesson, Do-It-Yourself (DIY) Guide, Stories and Additional Resources. Lessons will be ‘core reading’. They will educate patients about anxiety, low mood and depression; patients will read about unhelpful thoughts and behaviours, physical symptoms of depression and, towards the end of the course, relapse-prevention. DIY guides will provide patients with the opportunity to further their understanding of and begin to implement key concepts which are covered in the Lessons. The Stories will describe two examples of how others have learnt and practised those concepts. Additional resources will be optional reading; they will provide further information on specific topics which may help patients (for example, sleep, communication skills). Patients will be supported by weekly contact with their therapist involving up to five, 30-minute consultations. The first consultation will be face-to-face; the remainder will be by phone although we may accommodate patients’ specific requests for some or all of these to be face-to-face.

Stepped care participants’ progress will be monitored using the Patient Health Questionnaire 9 (PHQ-9)
[36]. At a sixth 30-minute consultation and following clinical assessment and discussion with the participant, people who show insufficient progress and/or who do not fall below the accepted PHQ-9 threshold for recovery (≤9)
[37] will be offered high-intensity psychological therapy. Participants who recover at this stage will only receive low-intensity therapy (see Table 
1).

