**Table 1 Tab1:** **Stepping criteria**

Pre-treatment score	Score at end of GSH	Criteria	Action	Decision
Any	0-9	Patient is unambiguously below diagnostic cut-off	Inform participant that treatment is ended as a consequence of them no longer meeting diagnostic criteria	Discharge
19-27	10-12	Patient is within suggested diagnostic cut-off range and has made around 50% improvement	Discuss with participant and suggest discharge due to good rate of progress	Step up or discharge depending on participant’s wishes
<19	10-12	Patient is within suggested diagnostic cut-off range and has made less than 50% improvement	Discuss with participant and suggest stepping up to increase progress further	Step up or discharge depending on participant’s wishes
Any	13-27	Patient is unambiguously above diagnostic cut-off	Offer CBT to participant	Step up

Criteria to determine if stepped care patients are discharged from treatment following guided self-help (GSH) or ‘step up’ to cognitive behaviour therapy (CBT).

High-intensity psychological therapy will be CBT delivered by therapists following a treatment protocol based on the standard manuals published by Beck and colleagues
[38] and used in two of our other recent trials
[30, 32]. Early sessions will focus on agreeing problems to be addressed, therapeutic goals and learning about the CBT model and techniques for behaviour change. Patients will subsequently work on negative automatic thoughts, maladaptive beliefs and, where indicated, underlying core beliefs. Later sessions will help patients anticipate and practice managing their response to stressors which could lead to future relapse. Specific CBT techniques that may be used will include scheduling activity and mastery behaviours and the use of thought records. All sessions will be face-to-face and consistent with National Institute for Health and Care Excellence recommendations for duration and frequency (that is, between 8 and 20, 50-minute consultations over a maximum of 16 weeks
[10]).

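### The stepping rule is stated two ways: the Stepped care text and Table 1 disagree for two groups of PHQ-9 scores, and the step-up proportion of research question 2 rests on that rule

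*Protocol article*

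**What the plan says.** Under Stepped care, the protocol article sets a sixth consultation at the end of guided self-help. After clinical assessment and discussion, "people who show insufficient progress and/or who do not fall below the accepted PHQ-9 threshold for recovery (≤9") are the group to be stepped up. The sentence and the one after it finish: "will be offered high-intensity psychological therapy. Participants who recover at this stage will only receive low-intensity therapy". The paragraph then points to Table 1.

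Table 1 (Stepping criteria) sorts patients by pre-treatment and end-of-self-help PHQ-9:

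- End score 0-9, any pre-score: "Inform participant that treatment is ended as a consequence of them no longer meeting diagnostic criteria". The decision is discharge.
- End score 10-12, pre-score 19-27: described as "Patient is within suggested diagnostic cut-off range and has made around 50% improvement". The action is "Discuss with participant and suggest discharge due to good rate of progress", and the participant decides.
- End score 10-12, pre-score below 19: described as "Patient is within suggested diagnostic cut-off range and has made less than 50% improvement". The action is "Discuss with participant and suggest stepping up to increase progress further", and the participant decides.
- End score 13-27, any pre-score: CBT is offered and the decision is step up.

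The proportions stepping up and discharged are research question 2, and the Quantitative analysis section plans to report them. The Discussion names the stepping criteria as a component of the intervention that has been defined.

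**The concern.** The text and the table describe one decision but do not always lead to the same advice. The text has two triggers for offering high-intensity therapy, joined by and/or: poor progress, or a score outside the recovery range. Table 1 has no progress trigger at 0-9, and at 10-12 it uses the pre-treatment score to choose between opposite suggestions.

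The step-up rate is one of the named uncertainties that the pilot is meant to resolve. The Background argues that existing services apply differing criteria, so that their data cannot supply a reliable rate for a large trial. The pilot's contribution is a rate observed under one stated rule. If the rule is stated two ways, the definitive trial cannot be sure which rule produced the observed rate, or which one to carry forward.

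**Working it through.** **Inputs.** The text rule is from Stepped care and the table rule from Table 1. The 1:1 allocation is from the Randomisation section and the total of 60 to 75 from Sample size. The protocol gives no expected step-up proportion, no margin of error for it and no PHQ-9 distribution, so there is no stated figure to reproduce. I take the recovery range as 9 or less, as Table 1 does.

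**Step 1: the two rules side by side, for every pair of PHQ-9 scores (0-27 before, 0-27 after).**

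| End score | Pre-score | Text | Table 1 | Agree? |
|---|---|---|---|---|
| 13-27 | any | offer | step up | yes |
| 10-12 | below 19 | offer | suggest step-up, participant decides | yes, in direction |
| 10-12 | 19-27 | offer | suggest discharge, participant decides | **no (advice)** |
| 0-9 | any, progress sufficient | low-intensity only | discharge | yes |
| 0-9 | any, progress insufficient | offer (and/or), but next sentence: low-intensity only | discharge | **no** |

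The first conflict covers 9 pre-scores × 3 end scores = 27 score pairs. The second cannot be counted from the document, because insufficient progress has no cut-off. If it is assumed to mean less than 50% improvement, 20 pairs with a pre-score of 10 or more qualify, for example 10 to 9 and 17 to 9.

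**Step 2: the improvement descriptors in Table 1.** Improvement = (pre − end) / pre.

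- Row 19-27 to 10-12: the lowest is (19 − 12)/19 = 36.8% and the highest is (27 − 10)/27 = 63.0%. Of the 27 pairs, 9 are below 50%.
- Row below 19 to 10-12: the highest is (18 − 10)/18 = 44.4%. Every pair is below 50%, so this label is correct.
- The bands cross at the edge. A fall from 19 to 12 is 7 points (36.8%) and leads to suggested discharge for good progress. A fall from 18 to 10 is 8 points (44.4%) and leads to suggested step-up. Four pairs in the upper row (19 to 12, 19 to 11, 20 to 12, 21 to 12) improve by less than 44.4%.

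**Step 3: precision of the step-up proportion.** The stepped care arm has 60/2 = 30 to 75/2 = 37.5, so about 30-38 patients. The 95% margin is 1.96 × √(p(1 − p)/n).

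| n | p = 30% | p = 50% |
|---|---|---|
| 30 | ±16.4 points | ±17.9 points |
| 38 | ±14.6 points | ±15.9 points |

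One patient is worth 1/38 = 2.6 to 1/30 = 3.3 points.

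**Step 4: possible effect on the proportion (illustration only).** Shift = share of patients in the conflicting zones × difference in step-up uptake between the two rules. If the share is assumed to be 10-20% and the difference 25-100 points, the shift runs from 0.10 × 25 = 2.5 points to 0.20 × 100 = 20 points. Both inputs are assumptions, and the width of the result shows that the document does not fix it.

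**The case against.** The best defence is that the paragraph is a summary and Table 1 is the rule. The text refers to the table, whose title and caption present it as the criteria for stepping. This is a natural reading and probably the intended one. But the article does not say that the table governs, and the summary is not a shortened form of it: in two zones it says something different.

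Three further points stand and limit the concern.

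- In both 10-12 rows the participant decides, and under the text an offer can be declined. Step-up is therefore open to these patients either way, and only the recommendation differs.
- The text's next sentence sides with Table 1 for recovered patients, so in the 0-9 zone the loose and/or is at odds with both.
- The row for pre-scores below 19 agrees with the text, and its improvement label is right for every pair. Rows are assigned by score, so the descriptors do not change which row a patient falls in.

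A reader might infer that therapists are following different rules, and that the step-up proportion could swing by the whole share of patients ending at 10-12, matching its own margin of error. The document does not support this. It does not say which text the therapists work from, and the clinical protocol is not shown. Patients who began below 19 are not in conflict. A full swing would also need every patient in the conflicting zones to step up under one rule and none under the other, although the choice at 10-12 is theirs.

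**Conclusion.** The concern holds in a limited form. The text and Table 1 disagree in two zones: pre-score 19-27 with end score 10-12, where the advice differs, and end score 0-9 with undefined insufficient progress, where the text also contradicts its own next sentence. Separately, one Table 1 descriptor is loose: the row described as about 50% improvement spans 37% to 63%, and at its edge a smaller improver is credited with good progress while a larger improver in the next row is advised to step up. Naming Table 1 as the governing rule would settle the two conflicts but not the descriptor.

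These are facts of the text and need no assumption. The size of any shift in the step-up proportion is not: it depends on a score distribution and uptake rates that the document does not give. The pilot tests no hypothesis on this proportion. What is at stake is that a quantity resting on 30-38 patients, already uncertain by about ±15 to ±18 points, should come from a single explicit rule.

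**What to change.** 1. Reconcile the Stepped care text with Table 1 and state which governs. This includes either defining insufficient progress or removing it as a separate trigger. Which rule is clinically right is for the investigators, and this review takes no view.
2. Make the descriptor of the row for pre-scores 19-27 agree with the scores that it covers.
3. For each stepped care patient, record the Table 1 row, the advice given and the final decision. Report the step-up proportion by row as well as overall, so that step-ups driven by the criterion can be told apart from those driven by preference in the 10-12 rows.

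The cost is one clarification and one extra field on the therapist form. The Trial status section says that recruitment is ongoing, so recording should start promptly. For patients already treated, the row can be recovered wherever both PHQ-9 scores were kept, but the advice given may not be.
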